## Methods

### Study design

This study will be a randomised controlled, double-blind, single-centre, clinical trial. This study protocol was written based upon the Standard Protocol Items: Recommendations for Interventional Trials (SPIRIT) guidelines (see Additional file 1) and will be carried out at an ICU of a hospital in the Brazilian public health system in the city of São Paulo, Brazil (Hospital Assembly of Mandaqui). Since the patients will be unconscious during the procedures, the oral-hygiene procedures will be conducted by researcher [name], together with a sample collection by researcher [name], both authors of this protocol study. This trial can be considered to be double blind. For better understanding, this study will be described in two phases, although two different studies will be performed, nested into each other. In phase 1, PDT with an MB mouthwash will be compared to PDT with MB in water, using chlorhexidine as positive control for oral hygiene. In phase 2, the frequencies of VAP occurrence will be measured in the two groups: (1) the most effective procedures found in phase 1 group and (2) the mechanical cleaning with filtered water group.

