### Randomisation

Randomisation will be conducted by a researcher not involved in the treatment of the patients ([name], author of this study protocol) when using Excel 2013 (Microsoft, Redmond, WA, USA). Opaque envelopes with sequential numbers will be used and a paper will be received containing the experimental group’s information according to the random draw. The envelopes will be sealed and stored in a safe place. [name] will be responsible for the storage and the confidentiality of the research envelopes. Immediately before the treatments, [name] will receive the envelopes from [name], open them (the first in sequence) and accomplish the indicated procedures.

#### Interventions in phase 1

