Within 24 h of the start of the mechanical ventilation and after checking the patients’ eligibility and obtaining the Consent Form signed by the person responsible for the patient, the intervention will be conducted. First, a patient’s sample will be collected by [name]. Following this, the oral-hygiene procedure will be performed by [name] with a gauze (7.5 cm × 7.5 cm size and sterile) soaked in a solution that will be determined by randomisation: (1) positive control group: chlorhexidine 0.12%, (2) MB 0.05% aqueous solution, (3) MB 0.05% blue mouthwash (this will be prepared in a pharmacy – the formula is under patent requirement). Oral hygiene will be initiated from the right upper arcade (the labial surface), passing to the left arcade (no return). Then, the palatal hygiene will be conducted from left to right. When the upper arch has been completed, the left buccal mucosa will be hygienised, then the lower arch moving from left to right. At conclusion, the mouth floor, the tongue and the lips will be hygienised (due to the dryness caused by the salivary reduction). After the mechanical cleaning and the active application of mouthwash, 5 min of incubation will be necessary before starting the light exposures. The light system will be a Lineaxul Bucal (Cosmedical, Brazil) which is a light-emitting diode (LED) device emitting at the red region of the spectra (660 nm). The device is a flexible lollipop-shaped instrument composed of six LED points on both sides, allowing for simultaneous illumination. Three devices will be used simultaneously: one above the tongue, promoting the illumination of the palate region and two others positioned on the buccal mucosa (right and left). Using this composition, the oral cavity will be illuminated as a whole for 15 min. Another sample will be collected by sterile swabs soaked in a physiological solution (sodium chloride 0.9%), 30 min after the procedure in the retromolar trigone region. These swabs will be stored in sterile tubes containing Tris-EDTA buffer (Tris 10 mM, pH 8, EDTA 1 mM) and will be identified with a patient number (received at randomisation) and a pre- and post-treatment label (T_0_ – before treatment; T_1_ – after treatment) [35]. Any modifications in the protocol will be informed in the results paper.

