### Outcomes

Phase 1: the main outcome will be the efficacy of the oral-hygiene procedures, evaluated by the total bacteria count, before and after the treatments (three groups and two time points). A secondary outcome that can be measured is the change in the pathogenic bacteria count that is related to VAP after the oral-hygiene procedures.

Phase 2: the main outcome will be the rate of VAP, evaluated by checking the medical cards, 5 days after the daily oral-hygiene procedures.

The detailed schedule for the study is presented in the SPIRIT figure (Fig. 3).

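### The trial is called double blind, but the operator opens the allocation envelope and nobody judging VAP is stated to be masked

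*Protocol article*

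**What the plan says.** The protocol article makes the blinding claim twice under Study design: "This study will be a randomised controlled, double-blind, single-centre, clinical trial" and "This trial can be considered to be double blind". The support offered there is that patients are unconscious and that one researcher performs the oral hygiene while another takes the samples. Trial status adds that the researchers' roles were revised so as to make the trial double blind.

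Under Randomisation, the list is produced independently: "Randomisation will be conducted by a researcher not involved in the treatment of the patients". Allocations are kept in sealed, opaque, numbered envelopes. Immediately before treatment, the person who will treat receives the envelopes and is to "open them (the first in sequence) and accomplish the indicated procedures".

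In phase 1 the solutions are chlorhexidine 0.12%, MB 0.05% in water and "MB 0.05% blue mouthwash". Each swab tube "will be identified with a patient number (received at randomisation") and carries a before or after label.

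In phase 2 the best phase 1 procedure is compared with mechanical cleaning using filtered water, daily for 5 days. The main outcome is the VAP rate, "evaluated by checking the medical cards". Under Interventions in phase 2, a diagnosis needs at least one of: oximetry (no threshold given), temperature outside stated limits, leukocyte count outside stated limits, or new, persistent or progressive infiltrates or pleural effusion. The article does not say who applies these criteria or whether that person knows the arm.

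**The concern.** Double blind is a claim about bias protection, and readers will credit the VAP comparison with it. The described procedure delivers masking for one party only, the patient, and that follows from sedation or illness rather than from the design. The operator is unmasked by the envelope step. The sample collector and the VAP assessor, whose masking would give the label its substance, are not said to be masked.

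The independent randomiser and the sealed envelopes protect concealment before allocation. They do nothing once the envelope is open.

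What is at stake is the phase 2 result. It rests on very few expected events taken from routine records, so a small amount of arm-dependent classification could create or remove the effect that the trial was sized to find.

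**Working it through.** **Step 1: who knows the arm, according to the article**

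| Party | What the article states | Consequence |
|---|---|---|
| Patient | Unconscious during the procedures (Study design) | Unaware of the arm |
| Operator | Opens the envelope and delivers the procedure (Randomisation) | Unblinded in every patient, both phases |
| Sample collector, phase 1 | A different researcher from the operator (Study design) | Masking not stated |
| Laboratory, phase 1 | Tubes carry patient number and time point (Interventions in phase 1) | Masking not stated; arm not on the tube |
| Bedside staff, phase 2 | Not mentioned | Masking not stated; colour could reveal the arm if an MB procedure is selected |
| VAP assessor, phase 2 | Nobody identified (Interventions in phase 2, Outcomes) | Masking not stated |

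The role split answers the question of who does what. It does not answer who knows what.

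**Step 2: how much judgement the phase 2 outcome allows**

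Temperature and leukocyte count have numeric limits. Oximetry has none, and deciding that an infiltrate is new, persistent or progressive needs a reader. Because one criterion is enough, a judgement on a single item can make a patient a case.

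**Step 3: how few records matter**

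The article gives no figure for the effect of unblinding, so there is none to reproduce. The calculation below only shows sensitivity. Inputs from Sample size calculation: planned proportions 0.086 and 0.041; 35 per group enrolled; 26 per group as the calculated requirement.

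Expected cases = n × p; shift from one record = 1/n.

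- Planned difference: 0.086 − 0.041 = 0.045, or 4.5 percentage points.
- n = 35: 35 × 0.086 = 3.0 and 35 × 0.041 = 1.4, a gap of about 1.6 cases. One record shifts a group's rate by 1/35 = 2.9 points (2.9/4.5 = 64% of the planned difference); two shift it by 5.7 points, more than the whole difference.
- n = 26: 26 × 0.086 = 2.2 and 26 × 0.041 = 1.1, a gap of about 1.2 cases. One record shifts the rate by 1/26 = 3.8 points (3.8/4.5 = 84%); two shift it by 7.7 points.

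So one record is most of the planned difference, and two exceed it.

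**The case against.** The strongest reply is that double blind may mean patient plus outcome assessor. An unmasked operator does not refute that reading, and the roles were revised for this purpose. The article also condenses a fuller protocol, and its SPIRIT checklist is an additional file not shown here, so assessor masking may be described elsewhere. This stands in part: on that reading the label is unsupported for assessors rather than disproved. It does not remove the point, because the article states the label, gives its grounds, and those grounds do not amount to masking.

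It can also be said that temperature and leukocyte limits leave little room for judgement. That is true of those two criteria, but not of oximetry as written or of the imaging criterion.

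A reader might infer more than the article supports:

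- **Swab labels reveal the arm.** They do not. The tube shows a patient number and time point, and the number gives the arm only to someone with access to the allocations. Laboratory masking is merely unstated, and the PCR count is an instrument reading.
- **The light reveals the arm.** Not established. Interventions in phase 1 describes illumination after the cleaning step and does not limit it to the MB groups.
- **Colour unblinds phase 1 throughout.** Both MB groups use 0.05% MB, so colour need not separate them, and nothing says how visible the dye is at the second swab, 30 minutes later.
- **Colour unblinds phase 2.** Only possible if an MB procedure is the one carried forward.

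**Conclusion.** The double-blind statement is inconsistent with the envelope procedure for the operator, in every patient and both phases. For the sample collector and the VAP assessor it is unsupported. The consequence is greatest for the phase 2 main outcome, where the planned difference is about 1.6 cases at 35 per group (about 1.2 at 26), so one or two records classified with knowledge of the arm could equal most or all of it.

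The size rests on the protocol's own planned rates and group sizes, and on the assumption that a record or two turns on judgement. The article neither shows nor excludes that. The finding is an exposure to bias that the label hides, not evidence that bias will occur. The colour route in phase 2 is conditional on an MB procedure being selected; the missing assessor masking is not.

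**What to change.** 1. In Study design and Trial status, replace the double-blind wording with a statement, for each phase, of who is blinded and who is not. The operator should be listed as not blinded.
2. For phase 2, have VAP status decided on record extracts from which allocation and oral-care notes have been masked, by an existing team member who neither delivers the procedures nor holds the envelopes. Name that role in Outcomes.
3. If step 2 is not adopted, drop the double-blind label.

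Trial status says recruitment has not started, so the change can be made before any patient is enrolled, and with the registry update already planned there. The cost is a less favourable label and some work to mask the extracts. Masked extracts do not undo any influence on what bedside staff wrote when they could see the arm, so if an MB procedure is selected that limit should be stated.

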### Sample size calculation

First, a published paper using the same method of sample analyses (PCR + PMA pre-treatment) is to be used to determine the effect size (*Δ*). The largest and the smallest mean values (1.69 and 0.27, respectively), as well as the standard deviation (*σ* = 0.36) of the PCR quantification of living bacteria using PMA were taken from the Àlvarez article, 2013 [50]. The *n* value is to be the number of treatment groups, i.e., 3:$$ \varDelta =\frac{Largest- smallest}{{\left(\frac{\sigma }{\sqrt{n}}\right)}^2}=\frac{1.69-0.27}{{\left(\frac{0.36}{\sqrt{3}}\right)}^2}=32.8 $$

G*Power software (version 3.1.9.2, Dusseldorf, Germany) was used to calculate the sample size. Using the calculated effect size, *F* tests will be chosen for the repeated measures and for the within-between interactions. Three groups will be studied and each group will be measured before and after the oral-hygiene procedures (i.e. three groups and two measurements). The sample size was determined by setting a two-sided error at 5% and the test power at 95% of the test. According to the calculations, a sample of six patients per group will be necessary in order to detect the differences in oral hygiene in phase 1. When considering this result and the possibility of difficulties in the sample processing, phase 1 will be conducted with 10 patients per group.

The sample size calculation for phase 2 was based on the percentages of patients with VAP before and after the implementation of oral-dental care, as published by Garcia et al. [8]. Using G*Power software, when choosing the Exact Family Test and Fisher’s Exact Test as statistical tests (inequality, two independent groups) and by inserting the proportions of 0.086 and 0.041 [8], the sample size was found to be 52, i.e. 26 patients per group. It is important to highlight that at this phase, a 5-day protocol will be evaluated. Due to the condition of the patients, some of them may recover and the mechanical ventilation will be removed, while some may get worst or even die. Due to these potential dropout patients, a sample size of 70 patients (35 per group) will be used.

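### The phase 1 effect size of 32.8 is not a Cohen's f, and six patients per group at 95% power does not follow from it

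*Protocol article*

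**What the plan says.** The point lies in the protocol article, Methods, Sample size calculation, first two paragraphs.

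- The inputs come from a published study that used the same assay: "The largest and the smallest mean values (1.69 and 0.27, respectively". The σ taken from that study is 0.36.
- The effect size is the difference of those two means divided by (σ/√n)², where the n "value is to be the number of treatment groups, i.e., 3". The printed result is 32.8.
- The test is then named: "Using the calculated effect size, *F* tests will be chosen for the repeated measures and for the within-between interactions". The design is given as "i.e. three groups and two measurements".
- The error rates were fixed by "setting a two-sided error at 5% and the test power at 95% of the test".
- The conclusion is that "a sample of six patients per group will be necessary in order to detect the differences in oral hygiene". The number is then raised to 10 per group to allow for problems in processing samples.

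No correlation between the before and after measurements is stated. The Data analysis plan section keeps the same repeated-measures ANOVA with interaction.

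**The concern.** G*Power's repeated-measures F test takes Cohen's f, a unit-free ratio of the spread of means to the within-group standard deviation. The printed formula has measurement units in the numerator and squared units in the denominator, and its n is not a sample size. A value of 32.8 is far outside any usual range for f. The sample size reported from it is also larger than such a value would give.

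Phase 1 chooses the procedure carried into phase 2, and its stated aim includes comparing the two methylene blue vehicles. A reader who takes the 95% at face value cannot tell what size of difference between arms it refers to. A non-significant interaction could then be over-read as showing that the arms perform alike.

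**Working it through.** **Inputs.** From Sample size calculation: means 1.69 and 0.27 (difference 1.42), σ = 0.36, 3 groups, 2 measurements, error 5%, power 95%, six per group (18 in total), planned 10 per group (30 in total). The pre-post correlation ρ is not stated; I assume 0.5 with a range of 0 to 0.8, and no nonsphericity correction.

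**1. The printed effect size.** 1.42 / (0.36/√3)² = 1.42 / 0.0432 = 32.87. The article prints 32.8; the rounding is immaterial.

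**2. Dependence on scale.** Multiply every measurement by 10: 14.2 / (3.6/√3)² = 14.2 / 4.32 = 3.29. The same data give a value ten times smaller, so this is not a standardised effect.

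**3. Standardised effect from the same inputs.** The range is 1.42/0.36 = 3.94 SD. For three means with that range, the between-group f lies between 3.94 × √(1/6) = 1.61 and 3.94 × √8/6 = 1.86. If the arms are equal at baseline and differ only after treatment, the interaction f is half of this: 0.805 to 0.93.

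**4. Power for the named test.** I use the noncentral F distribution with λ = f² × N × m/(1−ρ), m = 2, and degrees of freedom 2 and N−3 (G*Power's default convention for f).

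With f = 32.8, N = 6 and ρ = 0.5: λ = 1075.84 × 6 × 2/0.5 = 25,820. Power is about 1.00. It is also about 1.00 at 6 in total under other noncentrality conventions and for between-factor, within-factor and one-way tests. The smallest balanced design is therefore already enough: 6 in total, 2 per group. At 18 in total the power would be about 100%, not 95%.

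**5. Smallest balanced total for 95% power with a standardised f.**

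| f | ρ = 0 | ρ = 0.5 | ρ = 0.8 |
|---|---|---|---|
| 1.61 | 9 | 6 | 6 |
| 0.805 | 18 | 12 | 9 |

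The single cell equal to 18 (power 0.94 at 15 in total, 0.98 at 18) needs a halved f and a zero correlation, neither of which the article states.

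**6. What the sample sizes detect in the interaction test.**

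| Total | Power | f at ρ = 0 | f at ρ = 0.5 | f at ρ = 0.8 |
|---|---|---|---|---|
| 18 (6 per group) | 95% | 0.73 | 0.515 | 0.33 |
| 30 (10 per group) | 80% | 0.42 | 0.30 | 0.19 |
| 30 (10 per group) | 95% | 0.54 | 0.38 | 0.24 |

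At ρ = 0.5, power with 18 and 30 patients is 0.79 and 0.97 for f = 0.4, and 0.39 and 0.64 for f = 0.25.

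**7. Pairwise view.** For an unadjusted two-sided 5% t-test on change scores with 10 per group, the detectable difference is 1.33 SD of change at 80% power and 1.71 SD at 95%.

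**The case against.** The strongest reply is that a faulty derivation does not make the sample size wrong. This stands. If a difference of 1.42 with SD 0.36 really applied to the group contrast, f = 1.61 gives power of about 1.00 at 18 in total. Even the halved interaction f of 0.805 at zero correlation gives 0.98. A reader might infer that phase 1 is underpowered, or that its 95% could have no foundation at all; the documents support neither. What fails is the route from 32.8 to six per group.

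Three other readings are tempting and also go too far:

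- *Six was a total misread as a per-group number.* The arithmetic fits, but so does the route in step 5, and the article does not say which was taken.
- *Ten per group is offered as a comfortable power margin.* The stated reason is possible trouble with sample processing, which is an allowance for lost samples.
- *The 1.42 is an implausible difference between active agents.* The article does not say what the cited study compared, and that study is not at hand. The most that can be said is that its use for this interaction is not justified in the text.

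A separate analysis plan would not remove the problem, because the formula, test, software and result are all printed and do not fit together.

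**Conclusion.** The point holds as a fault in the printed derivation. The value 32.8 depends on the measurement scale, is not Cohen's f, and is 18 to 20 times the between-group f from the same inputs (32.87/1.86 = 17.7; 32.87/1.61 = 20.4). Used as f, it leads to 2 per group, not 6. The relevance of the borrowed means to a three-arm interaction is also left unargued.

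The conclusion on 32.8 does not depend on the unstated correlation, since power is about 1.00 at 6 in total even at ρ = 0 (λ = 12,910). The detectable effects at N = 30 do depend on it, which is why they are given as a range. Nothing here shows that 10 per group is too few. The change should be made, but it does not alter enrolment, allocation or analysis.

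**What to change.** In Sample size calculation, delete the effect-size formula, the value 32.8 and the six-per-group claim. Keep 10 per group and say what it detects for the planned interaction test at 5%. With 30 patients, Cohen's f (G*Power's default convention) for 80%/95% power is 0.42/0.54 at an assumed pre-post correlation of 0, 0.30/0.38 at 0.5, and 0.19/0.24 at 0.8. Name the assumed correlation and the convention for f.

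If a pairwise figure is wanted, give it in a separate sentence: about 1.3 SD (80%) or 1.7 SD (95%) of the change score on the analysis scale, unadjusted for the three comparisons. It should carry no correlation range, because in units of the SD of change it does not depend on the correlation. If the means from the cited study are kept, add a sentence on why they bear on differences in change between these arms.

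The cost is one rewritten paragraph and no extra patients. Trial status says that recruitment had not begun, so on that account the text can be corrected before the first patient enters.

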**Methods:**

Phase 1 will evaluate the most effective cleaning procedure, while phase 2 will correlate oral hygiene to VAP incidence. At the start of phase 1, the ICU patients will be randomly allocated into three different groups (10 patients/group): the efficacy of chlorhexidine, classical MB-PDT, and mouthwash MB-PDT will all be measured for the quantification of viable bacteria, both pre- and post-treatment, by a Reverse Transcription Polymerase Chain Reaction (RT-PCR). In phase 2, the most effective procedure found in phase 1 and a mechanical cleaning with filtered water will be carried out daily, once a day, over 5 days, with a total of 52 ICU patients randomly allocated into the two groups. The clinical records will be evaluated in order to find any pneumonic diagnoses.

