**Fig. 1 Fig1:**
[figure not shown]
Phase-1 flow diagram

#### Interventions in phase 2

Based upon the results generated in phase 1, a new group of patients will comprise phase 2 of this study. Here, the oral-hygiene procedures described above will be performed in two groups of patients: (1) the most effective procedures in phase 1 group and (2) the mechanical cleaning with filtered water group. These procedures will be performed daily, over 5 days, when the outcomes will be evaluated. The clinical records will be checked and the pneumonia diagnoses will be determined by at least one of the following criteria: oximetry; body temperatures above 38 °C or below 35 °C; a leukocytosis or a leukopenia (leukocytes) count in the peripheral blood that is below 4000/mm^3^ or above 11,000/mm^3^; the existence of new, persistent or progressive lung infiltrates, or pleural effusion [51–54]. If any of the patients present an adverse reaction, they will be removed from the study and this will be reported in the published results paper. All of the personal information of the patients will be kept confidential. Figure 2 will describe the complete flow diagram for phase 2.

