### Data analysis plan

The studied parameters in this work will aim to follow a Gaussian (normal) distribution and they will be verified by the Shapiro-Wilk test. Where the data are not parametric, they will be transformed by using a logarithm or any other math transformation into normally distributed data. In this manner, parametric methods will be used in order to detect the differences among the groups. In order to show the actual distribution of the measured data, a graph based on the mean values and standard deviations will be used. For the data analyses, SPSS Statistics^TM^ Version 22 Software (IBM, Armonk, NY, USA) will be used. The statistical analyses will be realised by using analysis of variance (ANOVA): this will include the repeated measures as well as the within- and between-group interactions since three groups will be studied and each group will be measured before and after the oral-hygiene procedures. The frequencies of VAP occurrence will be measured in the two groups: (1) the most effective procedures found in phase 1 group and (2) the mechanical cleaning with filtered water group. The chi-square test will be used to verify the difference between the observed frequencies. The significance level for all of the tests will be *p* < 0.05. The results of this study will be published in an international journal.

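### Phase 2 is sized on a before/after oral-care contrast, but the trial compares two forms of oral cleaning, and nothing in the protocol links the two

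*Protocol article*

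**What the plan says.** Under Sample size calculation, phase 2 is based on "the percentages of patients with VAP before and after the implementation of oral-dental care", taken from a published study. Fisher's exact test was run "by inserting the proportions of 0.086 and 0.041". The result is given as 26 per group (52 in total), raised to 35 per group (70) for dropout.

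The trial itself is described differently. Under Interventions in phase 2, "the oral-hygiene procedures described above will be performed in two groups of patients", daily over 5 days. The first group has the most effective phase 1 procedure. The Data analysis plan gives the other as "2) the mechanical cleaning with filtered water group". Study design and the Abstract name the same two arms.

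The Abstract's Methods also says that "phase 2 will correlate oral hygiene to VAP incidence".

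**The concern.** A before/after study of an oral-care programme contrasts the programme with whatever preceded it. Phase 2 contrasts two cleaning procedures that differ in the agent, and in light exposure if a photodynamic arm wins phase 1. If water cleaning has some effect of its own, both arms receive it, and it drops out of the difference.

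Two things are at stake. First, a sponsor who corrected only the calculation would still have a trial sized for another question. Second, a null result could be read as evidence that oral hygiene does not affect VAP, although phase 2 has no arm without oral hygiene and cannot show that.

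**Working it through.** **Inputs.** From Sample size calculation: rates 0.086 and 0.041, Fisher's exact test, two independent groups, 26 per group raised to 35. From the Data analysis plan: significance level 0.05. For phase 2, power and sidedness are not stated. I assume a two-sided test, and 80% power where a target is needed.

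**The plan's own figure.** With the pooled normal formula, mean rate 0.0635:

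n = [1.96·√(2·0.0635·0.9365) + 0.8416·√(0.086·0.914 + 0.041·0.959)]² / 0.045²
= (0.6759 + 0.2890)² / 0.002025 ≈ 460 per group (504 with continuity correction).

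The stated 26 per group does not follow from these inputs. Entering 0.86 and 0.41 does give 26 per group with Fisher's test (one-sided power 95.4% at 26, 94.4% at 25). A decimal slip is therefore possible but cannot be proven. It is a separate error from the one discussed here.

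**Power for the contrast actually tested.** Power is the sum, over all event counts x (control) and y (treated), of Bin(x; n, pC)·Bin(y; n, pT), counting only tables with two-sided Fisher p ≤ 0.05.

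The protocol does not say what share s of the fall from 8.6% to 4.1% is due to mechanical cleaning, so s is varied: pC = 0.086 − s·0.045, with pT held at 0.041.

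| s | pC | n = 35 | n = 492 | n = 784 |
|---|---|---|---|---|
| 0 | 8.6% | 2.1% | 80% | 95% |
| 1/4 | 7.475% | 1.2% | 57% | 79% |
| 1/2 | 6.35% | 0.6% | 30% | 47% |
| 3/4 | 5.225% | 0.3% | 10% | 15% |

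The sizes 492 and 784 are not in the plan. They are the sizes that give 80% and 95% Fisher power for 8.6% vs 4.1%, and they show what a corrected calculation on the same rates would leave unresolved.

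**Other directions.** The table fixes the treated rate and only lowers the control rate, so it shows one side. Others are possible:

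- 6.35% vs 1.85% (the agent adds a full 4.5 points on top of cleaning): 94% at 492 per group, 1.2% at 35.
- 6.35% vs 3.0%: 66% at 492 per group.
- 19% vs 4.1% (the Discussion cites a review with 25% falling to about 19% under oral hygiene): 33.5% at 35 per group.

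For 80% power against 4.1% with 35 per group, the control rate would have to be about 31%.

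**Precision at 35 per group.** At 8.6% vs 4.1%, SE = √(0.086·0.914/35 + 0.041·0.959/35) = 0.058. The approximate 95% half-width is 1.96·0.058 = 11.4 points, around a difference of 4.5.

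**Analysis test.** The Data analysis plan names another test: "The chi-square test will be used to verify the difference between the observed frequencies". The uncorrected chi-square test, enumerated the same way at 35 per group, gives 11.3% for 8.6% vs 4.1%. With about 3.0 and 1.4 expected events (35·0.086 and 35·0.041), that approximation is poor.

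**The case against.** A reader might go further and say that 8.6% vs 4.1% overstates the effect, or that 4.5 points is an upper bound. The documents do not support either statement. They do not describe care in the earlier period; if it already included basic mouth cleaning, 8.6% could be a fair proxy for the water arm. The phase 1 winner may do better than the source programme's 4.1%. The water-arm rate may also exceed 8.6%: the Discussion cites 19% to 25%, and the phase 2 diagnosis needs only one of several broad criteria. For the same reason the range 4.1% to 8.6% does not bound the water-arm rate. These points stand.

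It can also be said that at 35 per group the mismatch hardly matters, since power is 2.1% even on the plan's own rates. That is right for the trial as planned: the failure of 52 to follow from its inputs is the larger defect. But recalculating from the same two rates would not cure the mismatch.

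Last, the Abstract's phrase may be mere shorthand, since the same paragraph names both arms. That is fair, and a careful reader would not infer an arm without hygiene. The phrase still states a question that phase 2 cannot answer, and it is easily replaced.

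**Conclusion.** The mismatch holds on the text alone. The sizing rates describe a period before and a period after an oral-care programme, the trial compares two cleaning procedures, and no section explains why the rates carry over. The figure 0.086 is unsupported as the expected rate in the water arm, whichever way it errs.

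That the assumed effect is too large is probable, not shown. It rests on the protocol's own premise that oral hygiene lowers VAP, and on the assumption that water cleaning shares in that benefit. If half of the assumed fall came from cleaning and the treated rate stayed at 4.1%, a trial of 492 per group would have about 30% power instead of 80%. Under other assumptions power could be higher than nominal. At the planned 35 per group, Fisher power runs from well under 1% to about a third over the scenarios shown for that size.

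**What to change.** 1. In Sample size calculation, state that 0.086 and 0.041 are rates from before and after an oral-care programme, and do not present 0.086 as the expected rate in the water arm.
2. Give an assumed VAP rate for the water arm and one for the phase 1 winner, each over a justified range not confined to 4.1% to 8.6%. State sidedness and target power for phase 2.
3. Restate the power or detectable difference of 35 per group over that range, using the test planned for the analysis.
4. In the Data analysis plan, report the winner-minus-water difference in VAP rate with a confidence interval suited to small counts.
5. In the Abstract, replace the phrase about correlating hygiene with VAP by a statement that phase 2 compares VAP incidence between the selected phase 1 procedure and water cleaning, so that a null result is not read as no effect of oral hygiene.

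The cost is one recalculation and some wording, with no added patients or procedures; Trial status says recruitment had not started. The downside is a less favourable sizing rationale and a narrower claim.
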